## Abstract

**Background:**

Moderate sleep complaints are major gerontological issue affecting as many as 80% of older adults. More intriguing findings have indicated that moderate sleep complaints were associated with cognitive decline, functional deterioration, clinical depression, and even morbidity and mortality among older adults. The aim of this study is to evaluate the effects of an activity-based lifestyle intervention on moderate sleep complaint among community-dwelling older adults.

**Methods/Design:**

This sequential quantitative–qualitative mixed method study will randomly allocate 224 individuals to receive either the 16-week group-based moderate-intensity stepping exercise or 16-week health education. The exercise group receives three 60-min stepping exercises per week, whereas the education group receives weekly educative talks on health topics other than sleep. The primary outcomes are sleep quality as measured by the Pittsburgh Sleep Quality Index (PSQI) and sleep pattern as measured by the actiwatch. Physical fitness and mood status are measured as mediating variables by using the Rockport walking test and Profile of Mood States. The qualitative part will invite 30 individuals from the exercise group who have different sleep-related treatment responses to participate in individual interviews to explore their overall perception of using stepping exercise as a lifestyle intervention to improve sleep. Mixed effects model with intention-to-treat analysis will be used for quantitative data. Inductive thematic analysis with a prior coding framework will be used for the qualitative data.

**Discussion:**

By investigating the effects and the mediating mechanism of a moderate-intensity exercise program on moderate sleep complaints among older adults, this study will generate evidence of high scientific value and important public health implication. Understanding the sleep-promoting effects and acceptability of exercise informs how to apply lifestyle promotion as a public health practice to improve late-life moderate sleep complaints and forestall its progression to level of clinical severity.

**Trial registration:**

Clinical Trial Registry Team, Center for Clinical Research and Biostatistics CUHK, CCRB00491. Registered on 1 December 2015.

**Electronic supplementary material:**

The online version of this article (10.1186/s13063-018-2465-2) contains supplementary material, which is available to authorized users.

## Background

### Detrimental health impact of moderate sleep complaint

Sleep problems are a major issue in gerontological care, with as many as 80% of older adults reporting one or more sleep complaints, such as difficulty in falling asleep and nocturnal awakening [1]. Miles (1982) defined a single persistent sleep complaint or the co-occurrence of two or more sleep complaint as a condition called moderate sleep complaints [2]. The prevalence rate of this sleeping problem among older adults were found to be as high as > 40% [3].

It is a common misconception that moderate sleep complaints are an inevitable age-related change and are not counted as a health risk. However, increasingly more compelling evidence has indicated the detrimental effects of moderate sleep complaint in impairing memory and concentration [4], compromising social participation and functional performance, increasing physical symptoms, and increasing fall risk and mood disorders [4, 5]. More intriguing findings have indicated that moderate sleep complaints were associated with an increased risk of clinical depression, chronic diseases including dementia, healthcare utilization, and mortality [4, 6, 7].

## Is exercise an effective lifestyle intervention to promote sleep

An international guideline for health promotion states that intervention targeted at lifestyle factors is the best way to optimize the health of the aging population, as lifestyle intervention is perceived by older adults as more affordable, accessible, manageable, and readily applicable if it is integrated into their daily lives [8]. Exercise has been widely recognized as a lifestyle habit to promote better sleep. Indeed, traditional theories of sleep hypothesized that sleep serves the functions of temperature downregulation of the body and promotes energy conservation and body restoration [9]. Exercise, which elevates the body temperature and creates a metabolic expenditure, therefore triggers a stronger bodily need for sleep. The mood promoting effects of exercise also creates the prerequisite for high-quality sleep [9].

Despite the public recognition and theoretical assumptions on the sleep-promoting effects of exercise, research evidence on this topic is relatively less compelling. Driver and Taylor described this as an “Expectation-Evidence Paradox” [9]. There is a substantial amount of research which examined the sleep-promoting effect of acute exercise. A meta-analysis of 38 studies has identified its modest effect in improving the sleep architecture (e.g. slow-wave sleep) and acute exercise worked even less on improving sleep patterns (e.g. sleeping time, nocturnal awakening, etc.) [10]. It has been concluded that sleep patterns may respond slowly to the bodily metabolic changes. On the other hand, there is compelling evidence to indicate that people with a higher level of physical fitness or athletes reported much better sleep quality and pattern than their less-fit counterparts [9]. Physical fitness, which brings about improved autonomic response and enables higher daytime metabolic consumption, may render the body more readily for temperature downregulation and energy restoration and thereby trigger sleep.

Several pilot-scale studies, indeed, have examined the effects of chronic exercise which improved physical fitness among older adults with moderate sleep complaints. King et al. identified the therapeutic value of a 16-week moderate-intensity endurance exercise program in a randomized controlled trial (RCT) of 43 older adults who had moderate sleep complaints [11], as screened by the Sleep Questionnaire and Assessment of Wakefulness [2]. The program comprised two 40-min group-based training sessions on moderate intensity exercise and two home-based exercise sessions on brisk walking and stationary cycling per week. As compared with a sedentary control after 16 weeks, the exercise arm reported better sleep quality with a 1-h increase in sleep duration and a nearly 50% reduction in sleep-onset latency, after adjusting for their expected treatment credibility. As no sleep-promoting effect was detected at the eighth week of exercise practice, a longer practicing duration might be required to achieve the sleep-promoting effect. Ried et al. reported comparable findings in a sample of 17 sedentary older people and the improved sleep was associated with an improved physical fitness and mood status [12].

Despite such encouraging findings, King et al. failed to identify the sleep-promoting effects of a similar moderate-intensity training program on the objective polysomnographic measure [13]. The non-significant findings might be related to the undue stress caused by the polysomnographic assessment in the sleep laboratory. Another study also failed to identify favorable sleep-promoting effects of exercise of low intensity and shorter duration [14].

The “Expectation-Evidence Paradox” on the sleep-promoting effect of exercise urges for more stringent scientific evaluation of this lifestyle intervention. The positive findings from the pilot studies imply the need for full-scale RCT to examine the effect of moderate-intensity exercise on subjective and objective sleep measures. Future studies also need to avoid using black-box research, but to examine the mediating process between exercise and sleep, so that how and why this lifestyle intervention affects late-life sleep can be elucidated. Indeed, exploring the acceptability and perception of older adults on using exercise as a lifestyle intervention to improve sleep also facilitates the subsequent knowledge transfer. This study aims at addressing all these research agendas.

## Research aims and hypotheses

The primary aim of this study is to investigate the effects of moderate-intensity endurance exercise training on the sleep pattern and sleep quality of older adults who have moderate sleep complaints. The secondary aims include: (1) examining whether physical fitness and mood status functioned as mediating variables in the effect that the exercise training has on sleep; and (2) exploring the overall perception of older adults in using the exercise program as a lifestyle intervention to improve sleep, particularly the perceived effects, how and why exercise works or does not work, and acceptability, using a qualitative research approach (hence, no hypothesis). Figure 1 outlines the model used to tests mediation for physical fitness and mood status. The research hypotheses to be tested are as follow:

**Fig. 1 Fig1:**
[figure not shown]
Mediating process of exercise on sleep

For older adults with moderate sleep complaints,A 16-week moderate-intensity endurance exercise training has greater effect than a non-active attention placebo (i.e. a general health education program) in improving sleep quality and sleep pattern.The effects of the 16-week moderate-intensity endurance exercise training on sleep-related outcomes are mediated by an improved physical fitness and a reduced mood disturbance.

## Methods/Design

### Study design

This is a sequential mixed method study which includes a RCT with a waiting-list attention-controlled intervention to evaluate the effect of a 16-week moderate-intensity exercise training program on sleep quality and sleep patterns and the mediating variables. Older adults with moderate sleep complaints will be randomly allocated to receive either moderate-intensity exercise training or a general education program. The sleep-related outcomes and the hypothesized mediating variables will be measured at baseline before randomization and after completing the study interventions. Then, an individual qualitative interview with a purposive sample of 30 individuals in the exercise arm will be conducted to explore their overall perception of using exercise training for promoting sleep. Particular focus will be placed on how and why they perceive exercise to influence or not influence their sleep and their acceptability of this intervention. The qualitative findings will be used to enhance the interpretation of the quantitative findings about the effect and mediating process of exercise on sleep and to inform the application of the findings. The waiting list control group will receive the exercise training upon completion of the post-test data collection. Figure 2 outlines the overall study design and method.

**Fig. 2 Fig2:**
[figure not shown]
*Flow chart* of study and data collection plan

### Study settings and participants

The study will be conducted in six elderly community centers operated by three large-scale non-government organizations in Hong Kong. Eligible participants will be aged 60 years or above and have moderate sleep complaints, as assessed by the three-item Sleep Questionnaire and Assessment of Wakefulness (SQAW) [2]. The SQAW is a screening tool to identify moderate sleep complaints by assessing the frequency of having difficulties in initiating sleep, maintaining sleep, and early awakening on a “1–5” rating scale in an ascending frequency. A rating of ≥ 3 on any two items or a rating of ≥ 4 on any one item indicates the presence of moderate sleep complaints [2]. Exclusion criteria include participants with: (1) sleep disorder with an organic cause such as sleep apnea; (2) a medical problem (e.g. pain), responsible for the sleep complaint; (3) receiving sleep disorder treatment; (4) cognitive impairment as indicated by an Abbreviated Mental Test score of ≤ 6; (5) engaging in > 60 min per week of moderate or more vigorous exercise in the previous six months; and (6) acute muscular-skeletal problems, stroke, or cardiorespiratory disease including chronic obstructive airway disease and heart failure. A checklist has been developed to screen out the abovementioned exclusion criteria. As this study focuses on moderate sleep complaints, individuals who have reached insomnia of clinical severity according to DSM-V (labelled as insomnia disorder) will be excluded.

Power analysis is used to estimate the sample size estimation for pre-test–post-test study with attrition [15]. According to two pilot-scale studies which examined the effects of moderate-intensity endurance exercise on sleep among older adults [11, 13], the effect sizes of exercise interventions on sleep quality and pattern were in the range of 0.21–1.55 (Cohen’s d). Hence, this study aims to detect a small to medium effect size of 0.4 on the primary sleep pattern and quality outcomes. Using the program RMASS2, it is estimated that a sample size of n = 104 participants per study arm would give the study 80% power at a 5% level of significance to detect the targeted effect size of exercise, assuming randomization will render the two arms equal at baseline and allowing for a 10% attrition. As this study also aims at examining the mediating process between exercise and sleep, consideration is also given to the sample size requirement for path analysis using structural equation modeling approach. According to Loehlin, a sample size of at least 100 and preferable ≥ 200 is required to ensure the statistical power for conducting structural equation modeling [16] and thereby increasing the sample size to 112 individuals per study arm, in allowing for a 10% attrition, to attain the recommended total sample size of 200 participants (i.e. 112 × 0.9 = 100 per arm).

For the qualitative study component, a purposive subsample of 30 older adults who have reported different sleep-related response to exercise training will be invited for individual interviews. This sample size complies with various guidelines which recommend that a sample of 25 participants is adequate to reach data saturation [17, 18] and the sample of qualitative study should lie within 50 [19]. The change in the Chinese version of the Pittsburgh Sleep Quality Index (CPSQI) between the pre-test and post-test period is used as the pre-defined criterion, with ten older adults in each range of 0–35th percentile, > 35th–70th percentile, and > 70th percentile of the score to be selected. The individual selection will also maximize the variation in the socio-demographic background (including age, gender, educational level, and type of housing) within each percentile of the CPSQI score to allow a more comprehensive understanding of the phenomenon. If data saturation has not reached upon the completion of qualitative data collection from the 30 participants, one more case will be recruited from each percentile until no more new findings are detected.

### Study interventions

#### The 16-week moderate-intensity endurance exercise

The moderate-intensity endurance exercise training will be conducted by a research assistant with baccalaureate training in physical education or sport medicine (RA1). The co-authors ([name]) who are academicians in physiotherapy and exercise physiologist will conduct a three-day training course for the RA1. The exercise training is designed according to the recommendations of the American College of Sports Medicine (ACSM)’s position stand on Exercise and Physical Activity for Older Adults [20]. It is a moderate-intensity 7.5-cm-high bench stepping exercise program for seniors. It is a 16-week program, with three 60-min group training sessions (group size of around ten participants) per week. Each session starts with a 10-min warm-up period using stretching exercise and stationary mobilizing exercise for trunk and limb joints at both upper and lower bodies (e.g. shoulders, elbows, wrists, hips, knees, and ankles) and followed by a session of moderate-intensity endurance exercise. The duration of the endurance exercise will increase gradually from 20 min to the targeted 40 min over four weeks. The endurance exercise includes bench stepping exercise using a 7.5-cm-high stable wooden platform. This exercise has been shown to be very suitable for older people who are less physically active or have reduced joint flexibility and reduced bone strength [21]. Individuals will perform the bench stepping exercise in bouts of at least 10 min each (with a maximum of 5 min of rest in between the exercise bouts) to reach the targeted duration (i.e. 40 min of endurance exercise). Close monitoring and verbal encouragement will be provided by the attending RA1. Moderate-intensity exercise has been widely used among older people and is even safe for older patients with chronic diseases [22]. The Borg Rate of Perceived Exertion (Borg RPE) will be used to monitor the exercise intensity [23]. This is a 15-point scale with scores in the range of 6–20. Descriptors are attached throughout the scale with higher scores indicating more perceived exertion. Physical activity that results in a rating of 12–14 (descriptor: “somewhat hard”) on the Borg RPE is identified as reaching a moderate intensity [23]. The RA1 will explain the Borg RPE scale to the participants and instruct them to speed up or slow down their movements in order to achieve a feeling of “somewhat hard” at the Borg RPE rating of 12–14. The training session will end with a 10-min cool down session with walking exercise and stationary trunk and limb mobilizing exercise involving the joints of the shoulders, elbows, wrists, hips, knees, and ankles. The training will follow the ACSM safety guidelines with assessment done on blood pressure (BP) and heart rate (HR) and contradictory symptoms before training. Attendance rate and adverse events will be recorded.

#### The 16-week health education program

The health education program will be delivered as a non-active attention placebo by a part-time research nurse (RA2). It includes 16 60-min education sessions delivered on a weekly basis. Various health topics on home safety, brain health, foot care, flu prevention, medication management, aging and nutrition, common chronic illness among older adults, voucher scheme for elderly, smart grandparenthood, tips in choosing health screening, etc. will be included. No information relating to sleep and physical activity will be included. Upon the completion of the post-test data collection, the wait-list control group will receive the active study intervention for their sleep problem (i.e. the moderate-intensity endurance exercise program) within the study period.

### Issues of compliance

A previous study examining the effects of exercise therapy among Hong Kong older adults reported high compliance rate of around 80% for these two study interventions [22]. Various strategies, which are based on social cognitive theory and health belief model, will be used to optimize the individuals’ compliance. Table 1 outlines details of these strategies for promoting group cohesion, increasing perceived self-efficacy, and providing emotional and tangible incentives. The first author will provide a one-day training to the RA1 and RA2 on how to incorporate these strategies to the interventions. As the intervener–participant interaction may influence the treatment effect and is difficult to equalize between study arms, a 7-point semantic differential scale will be used to measure the individuals’ perceptions of the characters of the interveners including “friendliness,” “caring,” “sincerity,” “cheerfulness,” and “considerateness” during the post-test data collection. This captures any possible experimenter effect for statistical adjustment if necessary.

**Table 1 Tab1:** Strategies to optimize compliance to the study interventions

Strategies	Actions
Promoting group cohesion	- Group affiliation: Chinese titles will be assigned to exercise and health education program. Each class and participant will have an arm badge to signify their group identity. - Ice-breaking: Conduct two ice-breaking activities at the first training session to introduce the perception that they are “on the same boat” and have similar sleeping problems. - Goal-setting: The intervener facilitates the group to set the goal of achieving mean attendance rate of not less than 85% for each 2 weeks. The bi-weekly attendance rates will be presented graphically to the group and posted in the training room. - Group socialization: The intervener will foster communication between the participants to increase group socialization at the beginning and at the end of each training session.
Improving perceived self-efficacy	- Effective teaching: A step-by-step approach will be used to equip the individuals with the skills in conducting the intervention. The pace of teaching will be adjusted according to the participants’ learning needs. Clear instruction, demonstration, and return demonstration will be used as core teaching strategies. - Positive evaluation: The interveners will give positive evaluative feedback and encouragement to the individuals in each session.
Emotional and tangible incentives	- Motivational incentives: Three level of certificate awards will be presented to acknowledge the participants with a mean attendance rate of > 90% attendance at the 4th week, 10th week, and 14th week. The awards are titled as Certificate of Good Participation, Certificate of Good Perseverance, Certificate of Active Star, respectively. - Tangible incentives: A souvenir including magnifier, photo frame, coaster, sample hand cream, writing pad, or handkerchief will be provided to the awardees.

### Outcome variables

Sleep pattern and sleep quality are the primary outcomes whereas physical fitness and mood status are the secondary outcomes and mediating variables. The following methods will be used to measure these outcomes at baseline and upon the completion of training. Various potential confounders including demographic background, health profile, and expectation on treatment credibility will also be measured.

#### Sleep pattern

Sleep pattern refers to total sleep time (TST), time to initiate sleep (sleep latency [SL]), number and duration of wakening after sleep onset (WASO), and ratio of TST and the time spent in bed (sleep efficiency [SE]). These parameters will be measured by an actiwatch from the company called ActiGraph, which is a 3.5 × 3.5 × 1 cm watch. It contains an accelerometer to record the intensity and frequency of body movement during sleep. Individuals will wear the actiwatch on the non-dominant wrist during sleep for one-week’s continuous night monitoring. They are required to record the daily in-bed and out-bed time on a simple log book. To retrieve the parameters of sleep pattern, the actiwatch will be connected via a USB port to the ActiTrainer Online Management Platform. With the input of in-bed and out-bed time, an algorithm will translate the raw acceleration data to the sleep parameters. The actiwatch has extensive use in research and is well correlated with the findings on polysomnography [24].

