#### Sleep quality

Sleep quality is measured by the 19-item Pittsburgh Sleep Quality Index (Chinese version; CPSQI) [22]. Respondents rate their subjective sleep quality on a “0–3” Likert scale, with higher scores representing poorer sleep quality. The Cronbach’s alpha and test–retest reliability of the CPSQI are 0.82 and 0.77, respectively, with good discriminant validity when used in the Chinese population [25].

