### Data processing and analysis

Data will be double-entered for validation and analyzed on an intention-to-treat (ITT) basis. Skewed variables will be transformed before being subjected to analyses. Baseline characteristics between the two arms of participants will be compared using t test, chi-square test or Fisher’s exact test, as appropriate. Mixed effects models will be used to compare the differential changes on the primary (sleep pattern and quality) and secondary (physical fitness and mood status) outcomes across the baseline and post-test (T2) between the two study arms, with adjustment for the potential control variables (i.e. expected treatment credibility, demographic and health profile) which are statistically non-equivalent at baseline (*p* < 0.25). In particular, a dummy variable (group) will be assigned to represent the exercise training group (i.e. treatment group) with the health education group (i.e. control group) as reference, and another dummy variable (time) will be set to indicate the time points (1 = post-test, 0 = pre-test) in the mixed effects model. To accurately identify the effects of the exercise training, an interaction term group × time will also be included in the model to assess the difference in the change of each outcome across the pre-test and post-test period (i.e. pre-post change) between the two study groups. The statistical significance of the model coefficients, including the interaction term, will be assessed by Wald test. The strengths of mixed effects model lie in accounting for intra-correlation between repeatedly measured data and accommodating missing data caused by dropout, provided the data are missing at random [26]. This method is most suitable for ITT analysis without the need for missing data imputation. All analysis will be conducted by using SAS release 9.3 (SAS Institute Inc, Cary, NC) at a 5% level of significance. Depending on the data distribution, the mixed effects modeling will be performed using the PROC MIXED or NLMIXED.

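### Six sleep measures are all primary, each tested at an unadjusted 5%, with no lead measure or success rule, so neither the error rate nor the 80% power belongs to a defined trial result

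*Protocol article*

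**What the plan says.** - **Primary set.** Protocol, Outcome variables: "Sleep pattern and sleep quality are the primary outcomes whereas physical fitness and mood status are the secondary outcomes and mediating variables". Neither construct is ranked above the other.
- **Sleep pattern.** The section of that name lists the actigraphy parameters: "Sleep pattern refers to total sleep time (TST), time to initiate sleep (sleep latency [SL]), number and duration of wakening after sleep onset (WASO"), together with the "ratio of TST and the time spent in bed (sleep efficiency [SE"]). That is TST, SL, number of awakenings, duration of awakenings, and SE.
- **Sleep quality.** "Sleep quality is measured by the 19-item Pittsburgh Sleep Quality Index" in its Chinese version (CPSQI). The total is six measures, or five if WASO is taken as one.
- **Tests.** Data processing and analysis fits a group × time interaction, judged by a Wald test, to "assess the difference in the change of each outcome across the pre-test and post-test period".
- **Level.** The same section states: "All analysis will be conducted by using SAS release 9.3 (SAS Institute Inc, Cary, NC) at a 5% level of significance".
- **Hypothesis 1.** Exercise is to be better than health education "in improving sleep quality and sleep pattern". The article does not say how many measures must reach significance.
- **Sample size (Study settings and participants).** An effect of d = 0.4 on the primary outcomes, 80% power, one undivided 5% level and 10% attrition give 104 per arm. The rise to 112 is for the structural equation model, not for multiple testing.

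**The concern.** A trial result needs a rule that turns the test results into an answer. Here the set of primary measures and the level for each test are both fixed, but the rule that joins them is absent. If any one significant measure is enough, 5% is not the error rate of the trial. If both constructs are needed, 80% is not its power. Under either rule, sleep pattern still needs its own rule for its five parameters.

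A mixed result is foreseeable from the protocol itself. The Background reports one exercise trial with better reported sleep, and a similar programme that showed no effect on polysomnography. If the CPSQI improves and actigraphy does not, or if one parameter out of five moves, the protocol cannot say whether hypothesis 1 is supported.

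**Working it through.** **1. The plan's own figure.** Inputs from Study settings and participants: d = 0.4, 80% power, 5% level, 10% attrition.

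- Two-sided: n per arm = 2 × ((1.960 + 0.842) / 0.4)² = 98.1.
- With 10% lost at the second of two time points, averaged over both (my assumption about how the program treats attrition): 98.1 × (1 + 1/0.9) / 2 = 103.6, so 104. This matches the plan.
- Plain division of 99 by 0.9 gives 110. A one-sided 5% test gives 82 to 87. Neither matches.

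The article does not state sidedness, but its sample size fits a single two-sided 5% test.

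**2. Error if any one measure suffices.** This rule is assumed, because the protocol states none. Under no effect on any measure, with k independent tests:

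- Any significant difference, either direction: 1 − 0.95^k.
- Any significant difference favouring exercise: 1 − 0.975^k, because a two-sided 5% test puts 2.5% in each direction.

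| k | Either direction | Favouring exercise |
|---|---|---|
| 6 | 26.5% | 14.1% |
| 5 (WASO counted once) | 22.6% | 11.9% |
| 1 | 5% | 2.5% |

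For jointly normal statistics 26.5% is the ceiling in either direction. In the favourable direction the bound is 6 × 2.5% = 15% whatever the correlation.

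**3. Effect of correlation.** The protocol gives no correlations, so these are assumed values: six equally correlated normal statistics, 1,000,000 draws each.

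| Correlation | Either direction | Favouring exercise |
|---|---|---|
| 0.3 | 24.2% | 12.2% |
| 0.5 | 20.7% | 10.3% |
| 0.7 | 16.4% | 8.2% |
| 0.9 | 10.8% | 5.4% |

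With actigraphy measures correlated 0.6 among themselves and 0.2 with the CPSQI, the figures are 20.6% and 10.3%.

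**4. If both constructs must succeed.** With one test per construct, a false joint claim needs at least one true null to be rejected, so the error is at most 5%. Joint power lies between 0.80² = 64% (independent) and 80% (fully dependent). At 112 per arm, power per test is Φ(0.4 × √(n/2) − 1.96):

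- n = 112 × 0.9 = 100.8 gives 81.1%; squared, 66%.
- n = 112 / 1.0556 = 106.1 gives 83.0%; squared, 69%.

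The 5% bound fails if sleep pattern may succeed on any of its five parameters. If the CPSQI truly responds and the pattern does not, a false pattern result then has probability up to 22.6% (11.9% favouring exercise).

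**The case against.** - **The size can be overstated.** A reader might infer a 26% chance of falsely concluding that exercise improves sleep. The documents do not support that: 26% also counts false results against exercise. With two-sided tests the favourable part is about 14% under independence.
- **Independence is not realistic.** SE is computed from TST, and the actigraphy parameters share the same nights, so some correlation is certain. The 26% and 14% figures are upper values.
- **The any-of-six rule is not in the protocol.** A reader might take it as the trial's rule. The word joining the two constructs in hypothesis 1 could equally mean that both must succeed. It is one reading among several, and the missing rule is the defect.
- **Adjustment methods are often left to an analysis plan, and an article condenses.** The absence of a named procedure would therefore be weak evidence alone. But this text does fix the primary set and a 5% level for every analysis, and the choice of primary outcome and its success rule belongs in the protocol.
- **The 80% may be meant per outcome.** The sample-size text speaks of outcomes in the plural, and read that way the figure is correct. It then says nothing about the power to support hypothesis 1 as a whole.

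**Conclusion.** The point holds. Six measures (or five) are primary, each is tested at an unadjusted 5%, and no lead measure or success rule is stated.

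If one significant measure counts as success, a false difference in either direction has probability up to about 26%, or roughly 16% to 24% at assumed correlations of 0.7 to 0.3. A false result favouring exercise has probability of about 14% under independence, or roughly 8% to 12% over the same range. Against 2.5% for one two-sided test, that is a three- to almost six-fold rise.

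If both constructs must succeed on one test each, the error is controlled, but joint power can be as low as about 64%, or 66% to 69% at 112 per arm. The 80% is sound for a single test only. These figures rest on two-sided tests, normal statistics, d = 0.4 on each required measure, and correlations that the protocol does not give.

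**What to change.** Before outcomes are analysed, state the success rule for hypothesis 1 and pre-specify an ordered test at 5%. One example:

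1. CPSQI total score at 5%.
2. If significant, one named actigraphy parameter, such as SE, as the sleep-pattern primary at 5%.
3. The remaining actigraphy parameters (TST, SL, number and duration of awakenings) as a Holm-adjusted secondary family.

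The sponsor may choose another order or lead parameter. The protocol gives subjective and objective sleep equal standing, and its use of CPSQI change to select interviewees does not settle which comes first. Restate the 80% power as applying to the first test in the sequence.

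**Cost.** The remaining actigraphy parameters lose unadjusted primary claims, and the second test can be claimed only if the first succeeds. Ethical consideration requires committee approval before any protocol modification. Trial status reports recruitment still ongoing. The sample size and the power of the first test do not change.

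A Bonferroni split over six measures would cost more. At 0.05 / 6 = 0.0083, 80% power for d = 0.4 needs 152 completers per arm, and 112 enrolled per arm would leave about 58% to 61% power per measure.
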